### Statistical Analyses

An overview of statistical methods is given here, which can be adapted depending
on the data situation at the end of the study.

First of all, a summary of baseline data (eg, laboratory and anamnestic data) is
essential. Including the 95% confidence interval, categorical variables are
presented in absolute and relative frequencies and continuous variables are
described by the number of participants, mean, standard deviation, standard
error, median, minimum, and maximum.

Parametric and nonparametric tests will be used to compare quantitative variables
and frequency, and the chi-square test is applied on qualitative variables.
Furthermore the Kolmogorov-Smirnov test will be applied as a test of normal
distribution.

We expect the changes in HbA1c value in this study to follow a normal
distribution (based on previous other studies).^
34
^

Analysis of variance (ANOVA) is the main statistical method to analyze the effect
of the DHA on HbA1c as primary endpoint to show whether there is a significant
difference in primary outcomes between the two treatment groups.^
35
^ Data from both Visit 2 and Visit 3 will be compared with baseline data
from Visit 1. In addition, an ANOVA with repeated measures is performed, and
differences between participants as well as the number of visits and a possible
interaction between treatment and number of visits are represented by the linear
model.

Assuming a significance level of .05, ANOVA can be used to check whether the null
hypothesis can be rejected and which alternative hypotheses (Table 2) can be
accepted. Possible correlations are determined using the Pearson correlation
coefficient.

For multiple imputation of missing data, the jump-to-reference (J2R) method is
used, among others. To impute missing single HbA1c values, data from the
patient’s file of the treating HCP can be used as a substitute (as well as from
DHA of the IG). If no values are available here, the “Last mean carried forward”
method can be used.^
36
^

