#### Recruitment and randomization

Recruitment of the patients will take place in routine clinical practice in
several medical practices/study centers in Germany.

A simple randomization will be performed with the generation of a
randomization list.^
16
^ For this purpose, participating physicians will perform individual
randomization by screening potential participants for their inclusion
criteria by study personnel. After signing the informed consent form and the
anamnesis questionnaire, patients then will be randomized using the
predesigned randomization list.

Patients who meet all inclusion criteria will then receive an invitation to
the first visit by post. Later, participants of the IG will be asked to sign
another consent form to use the DHA.

As this is not a blinded study, the results of randomization cannot be hidden
from the study centers. The division into IG and CG will be obvious to staff
and participants.

Pseudonymization will be performed using a code that patients will receive
upon consenting to the study. The data will not be passed on to third
parties.

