### Measures and Questionnaires

Primary endpoint of the study is the change of HbA1c during the use of the DHA.
The main hypotheses are listed in Table 2. Measurement of the HbA1c
value, blood pressure, waist circumference as well as weighing and pregnancy
test will take place in every visit in both groups. Blood samples will be tested
in the local laboratory of each study site.

**Table 2. table2-19322968221075333:** Hypotheses of the Clinical Trial.

Hypothesis	Indicator	Relation
H0	Any	Is having no effect
H1	HbA1c	Is superior and has a clinical meaningful^ a ^ impact on lowering the HbA1c compared with standard diabetes care
H2	Hypoglycemic events	Is superior and has an impact on lowering hypoglycemic events compared with standard diabetes care
H3	Self-management	Is superior and improving self-management of diabetes patients compared with standard diabetes care
H4	Mental health	Is superior and reduces symptoms that represent a risk potential for secondary diseases such as depression compared with standard diabetes care

a HbA1c difference of 0.3 HbA1c % points.^20,21^

There will be several patient-reported outcome (PRO)^22-25^ questionnaires for
evaluating changes in empowerment, self-management, mental health, quality of
life, and other outcomes. The first questionnaire on personal data, medical
history, and inclusion criteria as well as all further questionnaires will be
completed via paper pencil.

All endpoints with matching questionnaires are listed and explained in Table 3.

**Table 3. table3-19322968221075333:** Predefined Endpoints.

Hypothesis	Primary endpoint	Data collection/questionnaire
H1	Change of HbA1c during the use of DHA	Data from HbA1c testing at the visit
Hypotheses	Secondary endpoints	Data collection/questionnaires
H1	Proportion of patients reaching their HbA1c treatment goals <7.0% during the use of DHA	Data from HbA1c testing at the visit
	Proportion of patients reaching their HbA1c treatment goals <6.5% during the use of DHA	
	Achieving a higher proportion of patients reaching the HbA1c treatment goals compared with CG	
H2	Frequency of severe and nonsevere hypoglycemic episodes (ADA recommendations: <70 mg/dL risk of hypoglycemic episodes, <54 mg/dL clinically important hypoglycemic episodes^ 26 ^)	Data from patient’s recollections (using DHA or Diary)
	Frequency of severe hyperglycemic events (ketoacidosis/nonketotic hyperosmolar coma)	Data from patient’s recollections (using DHA or Diary)

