#### Sample size calculation

The sample size calculation is performed with the program G*Power.^37,38^ It is
assumed that a reduction of 0.4 HbA1c % points (reduction from 8.0 to 7.6)
and an HbA1c standard deviation from 0.8 in the CG and 1.0 in the IG are
present. This assumption is based on the previous results of the analysis of
the AOK START (Systematic Trial with Analysis of Results in Telemedicine)
Project.^10,39^ This resulted in an effect size of 0.6625 and a
power of 0.95. With this assumption, a sample size of 77 participants in
each group (total of 154; dropout already included) will be necessary to
show a significant effect. A 20% drop-out rate is estimated based on the
experience of a previous study.^
34
^

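### The main analysis of HbA1c change is an ANOVA without baseline HbA1c as a covariate; adding it would raise precision at no cost, by an amount the protocol does not allow us to fix

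*Protocol article*

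**What the plan says.** The protocol article defines the primary endpoint under Measures and Questionnaires: "Primary endpoint of the study is the change of HbA1c during the use of the DHA". Under Statistical Analyses it names the method: "Analysis of variance (ANOVA) is the main statistical method to analyze the effect" of the app on that endpoint, with Visits 2 and 3 each compared with Visit 1. It then adds a second model: "from Visit 1. In addition, an ANOVA with repeated measures is performed, and" its terms are differences between participants, the visit, and a possible treatment-by-visit term ("interaction between treatment and number of visits are represented by the linear" model). Baseline HbA1c, diabetes type and site appear as covariates in neither model. The section describes itself as an overview that may be adapted to the data at the end of the study.

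The design does not force balance on these factors. Under Recruitment and randomization: "A simple randomization will be performed with the generation of a" list, with no strata. Type 1 and type 2 patients are both eligible, baseline HbA1c may run from 7.5% to 11.0% (Table 1), five sites are planned, and each site uses its own local laboratory.

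**The concern.** Analysing the change from Visit 1 does use the baseline value, but it subtracts the whole of it, as if a patient one point higher at baseline were expected to be exactly one point higher at follow-up. If the true slope is below 1, part of any chance baseline difference between the arms comes back into the estimate with the opposite sign, and the residual variance is larger than it need be. ANCOVA estimates the slope from the data instead.

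Two things are at stake: power, in a trial whose power at its own stated difference of 0.4 is not secure, and protection against chance imbalance, which simple randomisation of 154 patients does not give. The choice also needs to be made in advance. The trial is unblinded and the section leaves methods open to adaptation at the end, so a covariate added then could look data-driven.

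**Working it through.** **Inputs from the protocol article.** Difference 0.4 points; SD 0.8 (control) and 1.0 (intervention); power 0.95; 77 per group including 20% dropout (all from Sample size calculation). "Assuming a significance level of .05" (Statistical Analyses); two-sided is my assumption, and it is the one that reproduces the stated sample size. Clinically meaningful difference 0.3 (Table 2 footnote).

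**Inputs not in the article (assumptions).** The correlation ρ between baseline and follow-up HbA1c, taken as 0.3, 0.5 and 0.7. Whether the SD is that of the HbA1c level or of the change: both are shown. Equal SDs at the visits, relaxed in step 5.

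**1. The plan's own figure.** "This resulted in an effect size of 0.6625". A two-sample t-test (noncentral t) with d = 0.6625, two-sided 0.05 and power 0.95 needs 61 per group; 61/0.8 = 76.25, rounded up to 77. This matches, so the trial was sized for an unadjusted two-group comparison.

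**2. Power at the stated difference.** Pooled SD = √((0.8² + 1.0²)/2) = 0.9055, and d = 0.4/0.9055 = 0.442. With 61 completers per group, power is 67.7%. (The gap between 0.442 and 0.6625 is a separate matter.)

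**3. Variance of the two analyses.** With baseline SD s₀ and follow-up SD s₁:

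- change score: s₁² + s₀² − 2ρs₀s₁
- ANCOVA: s₁²(1 − ρ²)
- difference between them: (s₀ − ρs₁)², which is never negative

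So, apart from the one degree of freedom spent on the slope, ANCOVA is never less precise. With equal SDs s the two variances are 2s²(1 − ρ) and s²(1 − ρ²), with ratio (1 + ρ)/2.

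**4. Power with equal SDs**, 61 per arm, difference 0.4, one degree of freedom deducted for ANCOVA:

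| ρ | Ratio (1+ρ)/2 | SD is of level: change → ANCOVA | SD is of change: unadjusted → ANCOVA |
|---|---|---|---|
| 0.3 | 0.65 | 53% → 72% | 68% → 85% |
| 0.5 | 0.75 | 68% → 80% | 68% → 80% |
| 0.7 | 0.85 | 88% → 92% | 68% → 75% |

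For example, at ρ = 0.7 with the SD that of the level: change SD = 0.9055 × √0.6 = 0.701, d = 0.570; ANCOVA SD = 0.9055 × √0.51 = 0.647, d = 0.619.

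**5. Unequal SDs.** The entry range may narrow the spread at baseline. Assume s₀ = 0.7 and s₁ = 0.9055:

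- ρ = 0.5: change variance 0.676, ANCOVA 0.615, saving 9%
- ρ = 0.6: 0.549 and 0.525, saving 4.5%
- ρ = 0.7: 0.423 and 0.418, saving 1%

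Power then goes from 76% to 80%, 84% to 86%, and stays at 92%.

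**6. Chance imbalance.** If the SD is about 0.91 at both visits, the SE of the baseline difference with 61 per arm is 0.9055 × √(2/61) = 0.164, so its 95% range is ±0.32 points. The change score carries (1 − ρ) of this into the estimate: 0.22, 0.16 and 0.10 points at ρ = 0.3, 0.5 and 0.7, against a clinically meaningful difference of 0.3.

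**The case against.** The strongest reply has four parts.

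- **Nothing is invalid.** A reader might infer that omitting the covariates biases the result or spoils the test. It does not. Under simple randomisation the unadjusted ANOVA is unbiased over randomisations and keeps its type I error. Diabetes type and site are not stratification factors, so leaving them out does not make the standard error wrong either. This stands.
- **The size is not in the documents.** No correlation is given, the SD is not clearly of level or of change, and equal SDs are assumed. This also stands, and it is why only ranges are given. For type and site the article gives nothing to work with; if they explained 1% to 10% of the variance of change (an assumption), power at 0.4 would move from 68% to between 68% and 72%.
- **The repeated-measures model.** A reader might infer that this model dilutes the effect, because a treatment main effect that includes Visit 1 averages in a pre-treatment value. The section does not single out that test; the term it names is the treatment-by-visit interaction. With a constant effect of 0.4, compound symmetry and the SD read as that of the level, the two-degree-of-freedom interaction has 71%, 81% and 91% power at ρ = 0.5, 0.6 and 0.7. A reader might also infer that patients with a missing visit are dropped, but the same section plans multiple imputation and substitution of missing HbA1c values.
- **This is SAP detail.** The article is an overview, and an analysis plan not shown may name covariates. That would excuse silence. Here, though, the main method is named and the terms of the additional model are listed without baseline HbA1c, so the point concerns a stated choice.

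**Conclusion.** The point holds as a loss of precision that can be avoided at no cost. Its direction does not depend on ρ, on equal SDs or on how 0.9055 is read, because the variance difference is a square. Its size does depend on all three. With equal SDs and ρ from 0.3 to 0.7, the gain at a difference of 0.4 is 4 to 19 percentage points if 0.9055 is the SD of the level (92 − 88 to 72 − 53, rounded figures), and 7 to 17 if it is the SD of change (75 − 68 to 85 − 68). With a narrower baseline spread it can be close to nothing.

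The over-correction of chance imbalance holds whenever the true slope is below 1, as it is with equal SDs. Almost all of the gain that can be shown comes from baseline HbA1c.

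A reader might infer that adjustment would restore the planned 95% power. It would not in any of the cases tabulated: at a difference of 0.4 the highest is 92%.

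**What to change.** Make the primary analysis an ANCOVA of HbA1c at Visit 3 on treatment, with baseline HbA1c as a prespecified covariate. Using change as the outcome gives the same treatment estimate once baseline is in the model. Diabetes type and site may be added if named in advance, without claiming a particular gain.

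In the additional longitudinal model, use Visits 2 and 3 as outcomes, baseline HbA1c as covariate and treatment-by-visit terms, and name the treatment contrast at Visit 3 as the test.

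The cost is protocol and SAP wording, settled before outcome data are seen. Baseline HbA1c is already measured at Visit 1, and type and site are known at enrolment, so no patients, visits or procedures are added.

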## Methods

### Trial Design

A prospective, multicentric, randomized controlled trial (RCT) will be conducted
over a period of 6 months to investigate the effect of a DHA on HbA1c levels in
patients with type 1 and type 2 diabetes mellitus. To this end, we will compare
two groups of patients fulfilling the inclusion criteria (see Table 1): The control
group (CG) will only receive the standard diabetes care and the intervention
group (IG) will additionally use the DHA to monitor diabetes-relevant values
using various graphs and observe potential changes in these endpoints. Each
group will consist of at least 77 patients and will be supervised for a minimum
of 180 days. The schematic design of the DAVOS trial (E**V**aluation
**O**f the Impact of E**S**ysta on Hba1c in Patients with
Type 1 and Type 2 Diabetes mellitus in **DA**ily practice) is shown in
Figure 1.

**Table 1. table1-19322968221075333:** Inclusion and Exclusion Criteria in the DAVOS Trial.

*Inclusion criteria*
• Diabetes mellitus type 1 or 2 • ≥18 years old • Treated with insulin • HbA1c at baseline ≥7.5% and ≤11.0% • Not having used the investigated DHA in the past 12 months • Willing to use a smart glucometer and/or smart insulin pen • Internet access, smartphone/computer compatible with the DHA • Digital literacy to use a smartphone adequately
*Exclusion criteria*
• Using other apps linked to a BG meter or using an insulin pump or continuous glucose monitoring • Having used the investigated DHA in the past 12 months • <18 years old • Impairments (also mental impairments, eg, psychotic disorders) • Patients with home nursing (assisting BG testing) • Current participation in a weight loss program • Current participation in another study • Steroid therapy within the past three months (no exclusion criterion if used topically or inhaled less than five times a week) • Blood pressure ≥200 mm Hg at screening • BMI ≥40 kg/m² • Anemia (according to the WHO definition^ 15 ^) • GFR ≤40 mL/min • Current or planned pregnancy, breastfeeding women • Alcohol or drug abuse (within the past three months) • Employees of Emperra GmbH E-Health Technologies (or other institutions being involved in the trial)

Abbreviations: BG, blood glucose; BMI, body mass index; DHA, digital
health application; GFR, glomerular filtration rate; WHO, World
Health Organization.

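### ANOVA at .05 is named for all Table 2 hypotheses, including hypoglycaemic episodes (H2), whose frequency has no stated time base although 20% dropout is expected

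*Protocol article*

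**What the plan says.** In the Protocol article, Statistical Analyses makes ANOVA the main method for HbA1c, the primary endpoint. It then extends ANOVA to the whole hypothesis table: at .05, "ANOVA can be used to check whether the null hypothesis can be rejected and which alternative hypotheses (Table 2) can be" accepted. The wording is permissive. The same section allows parametric and nonparametric tests for quantitative variables and frequency, and introduces itself as an overview that may be adapted. It expects a normal distribution only for the change in HbA1c.

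Table 2 states H2 as "Is superior and has an impact on lowering hypoglycemic events compared with standard diabetes care". The matching secondary endpoint in Table 3 is "Frequency of severe and nonsevere hypoglycemic episodes", with reference to values below 70 and below 54 mg/dL. The source is "Data from patient’s recollections (using DHA or Diary"). No time unit or person-time denominator is given.

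On follow-up, Trial Design says each group "will be supervised for a minimum" of 180 days. Sample size calculation adds: "A 20% drop-out rate is estimated based on the" experience of an earlier study. That figure is overall, not by arm.

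**The concern.** Hypoglycaemic episodes are recurrent counts. They usually have many zeros, a long right tail and a variance that grows with the mean, so a comparison of means under normal theory is a poor default.

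The larger question is time at risk. A patient who leaves at day 60 with 4 episodes has a rate of 4 × 180/60 = 12 per 180 days, yet on totals scores better than a completer with 8. If such truncation is more common in one arm, that arm looks better for a reason unrelated to the app. Only the intervention group has to learn and use the app and its connected devices, and the trial is unblinded, so dropout that differs by arm is plausible, though the article does not predict it. At stake is a claim under H2 that totals could wrongly support, or an increase in episodes that they could make hard to see.

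**Working it through.** **Inputs from the Protocol article.** 77 per group (154 in total, dropout included); 20% dropout overall; 180 days; level .05. Sidedness is not stated. I take it as two-sided, so 2.5% in the favourable direction.

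**The plan's own figure.** A two-sample t-test with d = 0.6625, two-sided .05 and power 0.95 needs 61 evaluable per group, and 61/(1 − 0.20) = 76.25, rounded up to 77. The stated figure reproduces. It concerns HbA1c only. The article gives no event rate, dispersion or power for hypoglycaemia, so everything below rests on assumptions.

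**Step 1: expected ratio of totals.** Assume a constant event rate and leavers who exit uniformly over the 180 days. A leaver is then observed for half the period on average, and an arm with dropout d for a fraction 1 − d/2. So

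crude ratio = true rate ratio × (1 − d_IG/2)/(1 − d_CG/2).

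- 20%/20%: 0.90/0.90 = 1.00, no bias between arms.
- 30% intervention, 10% control (20% overall): 0.85/0.95 = 0.895, a spurious 10.5% reduction.
- 10% intervention, 30% control: 0.95/0.85 = 1.118, a spurious 11.8% increase.
- 40%/0%, the extreme split at 20% overall: 0.80/1.00 = 0.80.
- A true ratio of 1.5 at 30%/10%: 1.5 × 0.895 = 1.34.

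**Step 2: simulation across means and tests.** 77 per arm, negative-binomial episodes, mean 4, 10 or 20 per 180 days, dispersion 1 or 2, exit uniform from 2% of the period onwards, 500 runs per setting. ANOVA and a rank test on totals were compared with negative-binomial regression with a log(time) offset.

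| Setting | ANOVA | Rank test | Rate model |
|---|---|---|---|
| 30%/10%, no effect: false favourable | 4-10% | 5-14% | 2-3% |
| 30%/10%, true ratio 1.6: excess detected | 25-50% | 15-33% | 49-80% |
| 20%/20%, true ratio 0.6: power | 47-80% | 33-67% | 54-84% |

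In the last row the rate model gains about 5-8 points over ANOVA, setting by setting. With equal dropout the ANOVA error rate stays near 5%. At mean 10, dispersion 1 and 30%/10%, false favourable results were 9.6% for ANOVA against 2.8%, and a 1.6-fold excess was detected in 50% against 80%. A repeat of this setting gave about 8% against 2%, and 52% against 82%.

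**Step 3: simulation at a true ratio of 1.5.** 77 per arm, 600 runs. The false favourable rate is two-sided rejections minus rejections in the direction of excess. Power is ANOVA on totals / rate model.

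| Control mean, dispersion | No effect, 30%/10%: ANOVA false favourable | Excess detected, 20%/20% | Excess detected, 30%/10% |
|---|---|---|---|
| 2, 1.0 | 8.2 − 0.8 = 7.4% | 48% / 53% | 28% / 54% |
| 6, 1.0 | 9.3 − 0.5 = 8.8% | 60% / 65% | 38% / 64% |
| 6, 2.0 | 6.3 − 0.8 = 5.5% | 36% / 40% | 19% / 38% |
| 20, 0.5 | 13.2 − 0.2 = 13.0% | 87% / 92% | 61% / 93% |

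The 4-10% range therefore belongs to dispersion 1-2; less dispersed counts can exceed it. Monte Carlo error is about 1 point near 5% and 2 points near 50%. Here the rate model was given the true dispersion, which slightly favours it.

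**The case against.** The best defence is that the article fixes less than a literal reading suggests. ANOVA is only permitted for the Table 2 hypotheses, it is the main method for HbA1c alone, and nonparametric tests are available for frequencies. A frequency may be meant as episodes per day or week, and no sentence says that truncated totals will be compared. The jump-to-reference sentence is not limited to visit values, so the handling of leavers' counts is unspecified rather than shown to be raw. Denominators for a secondary endpoint are often left to an analysis plan. Completers have visits fixed at the start, day 90 and day 180, so the 180-day minimum adds little variation among them. Termination rates are themselves an endpoint, so a dropout imbalance would be visible. The numbers need an assumed imbalance, which could run either way, and the simulated data obey the model being recommended.

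Most of this stands, and it rules out stronger readings. A reader might infer that ANOVA alone decides H2; the text does not say so. A reader might also treat hypoglycaemia as the trial's main safety measure; Tables 2 and 3 present H2 only as a secondary superiority hypothesis.

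What does not fall is that a method is stated, and it reaches an event count with no time base. A rank test helps with skew but not with observation time. Leaving methods adaptable at the end of an unblinded trial leaves the choice of H2 test open after the data are seen.

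**Conclusion.** The point holds as a defect in a stated method, of moderate weight. ANOVA at .05 is named for hypoglycaemic episodes, the measure has no time base, and a fifth of patients are expected to leave.

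The size depends on two conditions that the article does not establish: that totals are compared, and that dropout differs by arm. If both hold at 30% against 10%, the crude ratio is 0.895 under no effect and false favourable ANOVA results are roughly 4-10% at dispersion 1-2 (13% in the one setting at 0.5). At a true 1.5-fold excess in the arm with more dropout, ANOVA falls 19 to 32 points short of the rate model. The reverse imbalance would bias against the app. If dropout is equal, there is no bias between arms and the cost is about 4-8 points of power. Event rates, dispersion, exit times and the split by arm are all assumptions.

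A reader might go further and conclude that the plan has a false H2 claim or a hidden excess built in. The documents do not support that: they give neither a rule to compare totals nor a dropout figure by arm.

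**What to change.** In Statistical Analyses, limit ANOVA to continuous endpoints. In Table 3, define the H2 measure as episodes per observed time. Analyse episodes below 70 mg/dL and below 54 mg/dL by negative-binomial regression with randomised arm as the term and log(days observed) as the offset, including all randomised patients up to their last recorded day. Report the rate per patient-year by arm and the rate ratio with a two-sided 95% confidence interval, so that an increase shows as clearly as a decrease. For rare severe events, report by arm the number of patients with at least one event and events per patient-year.

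The cost is a few sentences and slightly more analysis work; sample size and conduct do not change. It relies on event counts and on visit, app and diary dates that the planned data collection should supply. The small downside is that the rate model assumes a patient's rate before leaving represents the later rate. It does not address any difference between app and diary in how episodes are captured, which is a separate matter.

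### Missing HbA1c may be filled from an extra source in the intervention group only, and last mean carried forward and jump-to-reference are both allowed with no order between them

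*Protocol article*

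**What the plan says.** The Statistical Analyses section of the protocol article has two statements on missing data.

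- The general one: "For multiple imputation of missing data, the jump-to-reference (J2R) method is" used, with the qualification that it is one method among others.
- The one for single missing HbA1c values: data from the patient's "file of the treating HCP can be used as a substitute (as well as from" and then "DHA of the IG). If no values are available here, the" last mean carried forward method can be used.

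The treating health care professional's (HCP) file is named first and is open to both arms. The digital health application (DHA) is an added source and is confined to the intervention group (IG). The control group (CG) has no counterpart. The same section opens by saying that its methods may be changed in the light of the data at study end.

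Four other places bear on this:
- Trial Design fixes HbA1c at the start, day 90 and day 180.
- Measures and Questionnaires has HbA1c measured at every visit in both groups, with blood tested in each site's local laboratory. Table 3 gives visit testing as the source of the primary endpoint.
- Recruitment and randomization states that the trial is not blinded.
- Sample size calculation plans for 20% dropout.

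**The concern.** Two features of the rule are a problem if it is followed as written.

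First, the sources differ by arm. An IG gap can be filled from the DHA and a CG gap cannot. The Intervention group section describes the app and portal as carrying glucose and insulin data and does not mention laboratory HbA1c. It is therefore unclear what would be substituted, and whether it is the same measurement as the endpoint. Staff know the allocation, and no window or type of qualifying value is given.

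Second, the two imputation assumptions overlap. J2R gives lost IG patients the control profile. Carrying a mean forward assumes that nothing changes after the last visit, and it treats the filled value as observed. There are only two follow-up visits, so a patient lost after Visit 2 lacks exactly one value, at Visit 3. Both statements then apply to that patient and nothing ranks them. With one in five patients expected to be lost, the choice can move the primary estimate by an amount that matters against the 0.3-point difference in Table 2, and the plan allows it to be made once the data are known.

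**Working it through.** **The plan's own figure.** Inputs from Sample size calculation and Statistical Analyses: "This resulted in an effect size of 0.6625 and a" power of 0.95, significance level .05, dropout 20%. A two-sided two-sample t-test needs 61 per group, and 61/(1 − 0.20) = 76.25, rounded up to 77. The stated 77 reproduces, with the 20% loss included. (A one-sided test gives 51, then 64, and does not reproduce.)

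**Inputs for the illustration.**
- True Visit 3 difference D3 = 0.4 points (Sample size calculation).
- Missing share m = 0.20 (same section; its split by arm and timing is not given).
- Meaningful difference 0.3 (Table 2, footnote).
- Assumed, not in the document: the Visit 2 difference D2 is full (0.4) or half (0.2); the CG change c3 is 0, −0.2 or −0.4 at Visit 3, with c2 its value at Visit 2 (half of c3 when D2 is half, otherwise equal to it); a share f of those lost leave after Visit 2 and the rest before it.
- Assumed reading of last mean carried forward (LMCF), which the document does not define: a lost patient receives the arm's mean at the last attended visit, so a patient lost before Visit 2 receives zero change.

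**J2R.** IG mean change = 0.8 × (c3 − 0.4) + 0.2 × c3 = c3 − 0.32. CG mean change = c3. Difference = **0.32**, whatever c3 and f are.

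**LMCF, 20% lost in both arms.** Difference = 0.8 × D3 + 0.2 × f × D2 = 0.32 + 0.2 × f × D2.

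**LMCF, 20% of the IG lost and none of the CG.** Difference = 0.32 + 0.2 × c3 − 0.2 × f × (c2 − D2).

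| Loss | Timing | Other assumption | LMCF | J2R |
|---|---|---|---|---|
| Both arms | all after Visit 2 | D2 = 0.4 | 0.32 + 0.08 = 0.40 | 0.32 |
| Both arms | all after Visit 2 | D2 = 0.2 | 0.32 + 0.04 = 0.36 | 0.32 |
| Both arms | all before Visit 2 | none needed | 0.32 | 0.32 |
| IG only | all before Visit 2 | CG improves 0.2 | 0.32 − 0.04 = 0.28 | 0.32 |
| IG only | all before Visit 2 | CG improves 0.4 | 0.32 − 0.08 = 0.24 | 0.32 |

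**How far the range depends on the reading.** The two lowest values need LMCF to be applied to patients missing both Visit 2 and Visit 3. If single values is taken to mean that only Visit 3 is missing (f = 1), the scenarios run from 0.32 (IG-only loss, CG improving by 0.4 at Visit 3 and 0.2 at Visit 2, D2 = 0.2: 0.32 − 0.08 + 0.08) to 0.40.

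**A larger true difference.** The stated effect size does not match 0.4 points: the pooled SD is √((0.8² + 1.0²)/2) = 0.9055, and 0.6625 × 0.9055 = 0.60. That mismatch is a separate matter. At a true 0.6, J2R gives 0.8 × 0.6 = 0.48 and LMCF 0.40 to 0.60 over the same scenarios. The spread remains, but it no longer reaches 0.3.

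No figure can be put on the IG-only DHA source, because the document does not say what value it would supply or for how many patients.

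**The case against.** The strongest reply is that the two statements have different objects: J2R for dropouts, substitution and LMCF for isolated gaps. The section also calls itself an overview, and order and windows are commonly left to a fuller document. Much of this stands. A reader might infer that the LMCF rule contradicts J2R, but the text shows only overlap without an order. The overlap is nonetheless real for a patient lost after Visit 2. The IG-only source is a rule the article states, so it is not a detail left for later.

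A reader might also infer that gaps are filled only from an IG source. That is wrong, since the HCP file comes first and serves both arms.

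A reader might infer that the rule favours the app. The table does not support that as a general statement: LMCF can lie above, at or below J2R, and the document gives neither the timing nor the arm of dropout. Nor is the gap from J2R automatically bias. For a continuing user who misses one visit, a genuine laboratory value is closer to the truth than a J2R draw. One can reach 0.44 to 0.46 by filling every IG gap at the full effect (0.40) and every CG gap at a level before an improvement of 0.2 to 0.3 (0.20 × 0.2 to 0.3 = 0.04 to 0.06). That improvement is assumed, and the sum skips the HCP file.

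Finally, the endpoint wording, "Primary endpoint of the study is the change of HbA1c during the use of the DHA", might suggest an analysis of on-use data only. The fixed visits and testing in both groups largely settle that, and nothing restricts the analysis to on-use values.

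**Conclusion.** The point holds in limited form. The plan permits a substitute source for the primary endpoint in one arm only, in an unblinded trial, and it names two imputation assumptions without saying which governs a patient missing only Visit 3. The direction of bias cannot be determined from the document.

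At a true difference of 0.4 with 20% missing, the expected estimate is 0.32 under J2R and 0.24 to 0.40 under LMCF, on either side of the 0.3 meaningful difference. This rests on the assumed LMCF reading, the assumed timing and arm of loss and, at the low end, on applying LMCF to patients missing both follow-up visits. On the narrower reading the range is 0.32 to 0.40. These are shifts in the expected estimate. They do not show that significance would change. A narrower standard error is possible with single-value filling, but it cannot be sized while LMCF is undefined.

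**What to change.** For the primary analysis:

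1. Remove DHA-derived values and last mean carried forward.
2. Allow substitution only by a laboratory HbA1c from the HCP file, under the same rule and the same time window around day 180 in both arms, fixed in advance.
3. Handle every remaining missing Visit 3 value by J2R multiple imputation, and delete the qualification that it is one method among others.
4. Add a missing-at-random imputation as a sensitivity analysis.
5. Exempt these rules from the general permission to adapt methods to the data.

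Another single primary method applied equally to both arms would also close the gap. J2R is proposed because the plan already names it.

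The cost is wording, a possibly more conservative estimate (in the illustration up to 0.40 − 0.32 = 0.08 points lower) and a somewhat wider confidence interval. No change to visits or data collection is needed.
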